#### LRE-BFR

The participants will undergo a 30-min LRE-BFR (with TheraBand elastic bands) intervention three times a week for 12 weeks. The 30-min intervention will consist of a 5-min warm up, 20-min LRE-BFR and 5-min relaxation period. The exercise load will be set to 20%–30% of 1RM, based on Cook et al. [32] and the ACSM [33]. Each session will be composed of four sets of 30–15-15–15 min, with a rest of 30–60 s between sets. The three resistance movements will be bicep bends, seated rows and seated knee extensions, and each movement must be held for 3 s until the end.

Nylon cuffs inflated with an inflatable pump (TD312 Hokanson™, Bellevue, USA) will be tied to the proximal end of the two lower limbs of a participant at 50% LOP [34]. The individualised LOP will be determined before the start of the intervention. A vascular doppler probe (DV-600, Marted, São Paulo, Brazil) will be used to detect the participants’ lower limb tibial artery whilst resting in a horizontal position. The pressure at which the nylon cuff will be inflated until the arterial auscultation disappears will be the LOP [35]. The nylon cuff should be continuously inflated and not cause discomfort throughout the intervention.

#### CRE

The participants will undergo a 30-min CRE (with TheraBand elastic bands) intervention three times a week for 12 weeks. The 30-min intervention will consist of a 5-min warm up, 20-min conventional-load elastic band intervention (60%–70% of 1RM) and 5-min relaxation period. The number of repetitions, rest duration and movements will be the same as those in the LRE-BFR group.

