#### Muscle strength of lower limbs

Lower limb muscle strength is reflected by the KES, which is assessed by the estimated 1RM. The standard 1RM test has exercise injury risks for older people [36]; therefore, the estimated 1RM test will be used to measure the exercise load. The exercise load will be measured in kilograms, with the participant sitting in an extensor chair equipped with a weight plate with an initial load of 45% of the body weight for women and 64% of the body weight for men [37, 38]. If the participant can perform knee extensions > 10 times with the initial weight, then the plate weight should be increased until the participant can repeat the exercise 10 times or less, at which the submaximal weight will be set as the weight of the plate. The following calculation formula will be used: estimated 1RM (kg) = submaximal weight (kg)/(1.0278—maximal repetitions*0.0278) [39].

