Lastly, this study will evaluate the efficacy of LRE-BFR in reducing CVD risk factors to explore its implications on the cardiovascular health of older people with SO. Although LRE-BFR is a novel intervention strategy for managing the physical health of older people [50], evidence on its cardiovascular safety is lacking, especially for older people with CVD risk factors. An 8-year cohort study on people aged ≥ 65 years found that older people with SO have a significantly increased risk of CVD by 23% compared with older people with no SO [9]. Exploring the potential impact of LRE-BFR on cardiovascular health is essential if LRE-BFR is to be widely promoted among older people with SO.

Although BFR can offer new ideas for exercise interventions, limitations remain in its use. Existing studies focused little on the safety of LRE-BFR, especially for frail older people. The exercise prescription design of this study is based on the BFR exercise guidelines [61] and ACSM resistance exercise recommendations for older people [33], which are generalisable. However, whether it is an effective exercise prescription for older people with SO remains unknown. Cook et al. [62] observed that muscle fatigue induced by LRE-BFR (20%–40% of 1RM) is similar to or higher than that induced by high-load (80% of 1RM) resistance exercise. Although fatigue may stimulate an increase in muscle mass or strength, it may decrease the compliance of older people with SO. Therefore, we will constantly monitor the participants’ fatigue in our study and conduct timely adjustments of the exercise prescriptions, when necessary, to decrease the injury risk of the exercise interventions.

For older people with SO, LRE-BFR is a novel exercise mode whose efficacy has yet to be investigated. By comparing the effects of LRE-BFR and CRE, our study will contribute an easy-to-perform and efficient mode of exercise that will enable clinical staff and researchers to effectively manage older people with SO.

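### The CRE arm is given the 30-15-15-15 repetition scheme at 60–70% of 1RM; the protocol's own 1RM equation strongly indicates that load and repetitions cannot both be met, and nothing says which gives way

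*Protocol article*

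**What the plan says.** - **CRE section.** The arm receives a "20-min conventional-load elastic band intervention (60%–70% of 1RM"), and "The number of repetitions, rest duration and movements will be the same as those in the LRE-BFR group".
- **Group protocols, Table 2.** One scheme is listed for both exercise arms in every phase: 4 sets of 30, 15, 15 and 15 repetitions, with rests of 30, 45 and 60 s by phase. Only intensity separates the arms: 20/25/30% of 1RM for LRE-BFR and 60/65/70% for CRE.
- **LRE-BFR section.** "The exercise load will be set to 20%–30% of 1RM", and the sets are described as "four sets of 30–15-15–15 min". The unit is minutes here but repetitions in Table 2.
- **Muscle strength of lower limbs.** Knee extensor strength, a primary outcome, is obtained from "estimated 1RM (kg) = submaximal weight (kg)/(1.0278—maximal repetitions*0.0278"), with the plate weight raised until the participant manages ten repetitions or fewer.
- **Discussion.** Fatigue will be monitored and the team will "conduct timely adjustments of the exercise prescriptions, when necessary".

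The article gives CRE no other repetition scheme and no rule for a set that cannot be completed.

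**The concern.** A scheme with a 30-repetition opening set is paired with loads two to three times those of the arm it was written for. The equation that defines 1RM in this trial ties load to repetitions to failure, so it offers an internal check on whether the pairing is feasible. If it is not, either load or repetitions must give way, by an amount that may differ between participants.

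The second objective is to compare CRE with LRE-BFR. If load is cut, the comparator is no longer at 60–70% of 1RM. If repetitions are cut, the arms are no longer matched on repetitions as stated. With 11 participants per group, a finding that LRE-BFR does as well or better might reflect an under-delivered comparator. The conflict also reaches the main endpoint: knee extension is one of the three trained movements, and knee extensor strength is the basis of the sample size.

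**Working it through.** The protocol states no figure for repetitions to failure, so there is none to reproduce. The check uses its own equation.

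**Inputs.** Equation: 1RM = w / (1.0278 − 0.0278 × r), where r is the maximal number of repetitions (Muscle strength of lower limbs). Loads and repetitions: Table 2.

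**Step 1. Solve for repetitions.** r = (1.0278 − w/1RM) / 0.0278.

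| Arm | Load (% 1RM) | Implied maximum r | 30 ÷ r | Is 15 within r? |
|---|---|---|---|---|
| CRE, first phase | 60 | 0.4278/0.0278 = 15.4 | 1.95 | just, if fresh |
| CRE, second phase | 65 | 0.3778/0.0278 = 13.6 | 2.21 | no |
| CRE, third phase | 70 | 0.3278/0.0278 = 11.8 | 2.54 | no |
| LRE-BFR, first phase | 20 | 0.8278/0.0278 = 29.8 | 1.01 | yes |
| LRE-BFR, second phase | 25 | 0.7778/0.0278 = 28.0 | 1.07 | yes |
| LRE-BFR, third phase | 30 | 0.7278/0.0278 = 26.2 | 1.15 | yes |

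At 60% a single fresh set of 15 is just inside the limit, but here three such sets follow the opening set with 30 s rests.

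**Step 2. Invert the other way.** Fifteen repetitions correspond to 1.0278 − 15 × 0.0278 = 0.611 of 1RM, and 30 repetitions to 1.0278 − 30 × 0.0278 = 0.194.

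**Step 3. How far is this from the tested range?** Ten repetitions correspond to 1.0278 − 0.278 = 0.750 of 1RM. From that edge, the equation adds (0.7498 − 0.70)/0.0278 = 1.8 repetitions at 70% and (0.7498 − 0.60)/0.0278 = 5.4 at 60%. For 30 repetitions to be the true maximum, 20 would have to be added instead: about 11 times the equation's gain at 70% (20/1.8) and 3.7 times at 60% (20/5.4).

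**Step 4. The rest of the schedule.** Taken as minutes, the sets total 30 + 15 + 15 + 15 = 75 min inside a 20-min exercise block, whereas Table 2 heads the same numbers as repetitions. Week 8 lies in both the 5–8 row (45 s rest; 25% and 65% of 1RM) and the 8–12 row (60 s rest; 30% and 70%).

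**The case against.** The strongest reply is that the equation is being asked to do more than the protocol asks of it. It estimates 1RM from at most ten repetitions, for knee extension on a weight-plate chair. Training uses elastic bands chosen from a force–elongation table, with perceived exertion also used to set the load, and includes biceps bends and rows, for which no 1RM method is given. Read literally, the equation also rules out 30 repetitions in the LRE-BFR arm, by 0.2 to 3.8 repetitions. All of this stands, and it means that the inversion cannot prove the CRE scheme undeliverable. It does not remove the conflict: the CRE limits of about 12 to 15 lie just beyond the tested range, and the gap is roughly two-fold or more, against 1–15% for LRE-BFR.

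The adjustment clause in the Discussion may seem to resolve the matter. It does not, because using it means leaving the stated load or the stated repetitions, and it does not say which.

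A reader might infer several stronger points that the text does not support:

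- *The session overruns its 20-min block.* With a 3 s hold on every repetition and four sets per movement, the last phase takes 3 × 75 × 3 s + 9 × 60 s = 1,215 s, or 20.25 min, an excess of 15 s. Both readings are unproved. With four sets per session, as the LRE-BFR text literally says, it is 75 × 3 s + 3 × 60 s = 405 s, or 6.75 min.
- *Delivered dose will go unrecorded.* Perceived exertion and attendance are to be recorded, and an article need not list session-log fields.
- *Participants are driven to repeated failure.* No passage instructs this, and supervision and fatigue monitoring are promised.
- *The randomised comparison becomes invalid.* The intention-to-treat contrast of assigned regimens stands. What weakens is its attribution to a delivered load.

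**Conclusion.** The concern holds as an internal conflict between the CRE section and Table 2 on one side and the 1RM equation on the other. The first CRE set is about 2.0, 2.2 and 2.5 times the implied maximum in the three phases, and the 15-repetition sets exceed it in the second and third. Load and repetitions are therefore unlikely both to be met, and the document does not say which yields. A similar or better LRE-BFR result could not then be read as a comparison with exercise delivered at 60–70% of 1RM.

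This assumes that the equation holds approximately for a few repetitions beyond ten, and that it is a fair guide to banded knee extension; it says nothing direct about the other two movements. A reader might go further and call the comparator impossible to deliver, but the equation's range and its LRE-BFR result do not support that certainty. Confidence is moderate. The unit slip and the week 8 overlap are real but editorial, and add no weight to the main point.

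**What to change.** Before the first session, the investigators should:

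1. Reconcile Table 2, the LRE-BFR and CRE sections and the 1RM equation on CRE load and repetitions.
2. State which of load or repetitions governs when both cannot be met, so that adjustments follow a stated rule.
3. Commit to reporting the load and the completed repetitions delivered in each exercise arm.
4. In the same edit, reconcile the minutes in the LRE-BFR section with the Repetitions column of Table 2, and assign week 8 to one row.

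Which scheme is right, including whether the arms should share one, is for the clinical team. The cost is an amendment to one table and a few sentences, plus a reporting commitment. Sample size, outcomes and analysis model are unaffected. Once sessions have begun, an undefined comparator cannot be repaired by analysis.

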#### Control group

The participants in the control group will not be given any exercise intervention but will participate in a weekly 20-min health education session on the meaning of SO, its risk factors and its adverse health outcomes. The International Physical Activity Scale Questionnaire-Short Form will be collected weekly to ensure that the participants are maintaining their daily PA level.

#### Nutritional intake

During the 12-week intervention and 12-week follow-up period, the researchers will require all the participants to maintain their daily dietary habits. The participants will be interviewed by professional researchers and community workers over the telephone regarding their diet (e.g. protein and fat intake at three meals a day), which will be recorded in a specific notebook. The frequency of the telephone interviews and monitoring will be 3 times a week (twice on weekdays and once on weekends), and the conversations will be recorded.

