### Interventions

#### Group protocols

Before the formal interventions, the participants in the LRE-BFR and CRE groups will undergo 1RM testing and be taught how to use the Borg rating of perceived exertion (RPE) scale ranging from 6 to 20 to determine the target resistance load, and the RPE scores during the intervention will be recorded. The exercise intensity will be set based on the TheraBand force–elongation table to select the appropriate elastic band, which is reflected in the elastic band colour, from yellow to red to green. Limb occlusion pressure (LOP) testing will be performed in the LRE-BFR group. The participants’ attendance and occurrence of any adverse effects during the exercise interventions and follow-up period will be recorded by a dedicated investigator. If a participant misses a planned exercise intervention, they will make up the session at another time during the same week. All the participants will have three preintervention sessions to familiarise themselves with the exercise flow. The intervention protocols for the three groups are presented in Table 2.

**Table 2 Tab2:** Details of the three groups of protocol

Weeks	Group	Specific intervention content	Sets	Repetitions	Interval rest time between sets (s)	Intensity	Frequency (times/week)
1–4	LRE-BFR	Biceps bend, seated row, seated knee extension	4	30,15,15,15	30	20% 1RM	3
	CRE					60% 1RM	
	CG	Education session (no intervention)	/	/	/	/	1
5–8	LRE-BFR	Biceps bend, seated row, seated knee extension	4	30,15,15,15	45	25% 1RM	3
	CRE					65% 1RM	
	CG	Education session (no intervention)	/	/	/	/	1
8–12	LRE-BFR	Biceps bend, seated row, seated knee extension	4	30,15,15,15	60	30% 1RM	3
	CRE					70% 1RM	
	CG	Education session (no intervention)	/	/	/	/	1

*LRE-BFR* Low-load resistance exercise with BFR, *CRE* Conventional-load resistance exercise, *CG* Control group, *1RM* One-repetition maximum

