#### Safety monitoring

We are professionally trained to fully supervise and guide the participants during the exercise intervention to reduce their risk of injury. We are obligated to report the occurrence of any adverse effects during the intervention to the local ethics committee and work together to find the best solution. The participants have the right to terminate their participation in succeeding experimental interventions.

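### No common way of asking about adverse events in all arms is described, and exercise participants have 36 sessions against 12 for controls in weeks 1–12; one identical question on an existing weekly diet call would even this out.

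*Protocol article*

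**What the plan says.** **Recording.** Under Group protocols, the "occurrence of any adverse effects during the exercise interventions and follow-up period will be recorded by a dedicated investigator". Table 1 marks adverse events for weeks 1–12, week 12 and week 24 and does not split them by arm.

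**Supervision, reporting and storage.** Safety monitoring says that trained staff will "fully supervise and guide the participants during the exercise intervention" and that they must "report the occurrence of any adverse effects during the intervention to the local ethics committee". Data management and monitoring likewise refers to adverse effects in the intervention period. Neither section mentions follow-up.

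**Contact by arm.** Each exercise arm has an "intervention three times a week for 12 weeks" (the words are from CRE; LRE-BFR has the same frequency). Controls receive no exercise and "will participate in a weekly 20-min health education session". Also for controls, "The International Physical Activity Scale Questionnaire-Short Form will be collected weekly"; its stated purpose is to check that activity stays at its usual level.

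**Telephone calls.** Nutritional intake asks all participants to keep their diet unchanged over the 12-week intervention and the 12-week follow-up, and provides for telephone interviews about diet: "The frequency of the telephone interviews and monitoring will be 3 times a week (twice on weekdays and once on weekends". No adverse-event question is mentioned for these calls.

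**The concern.** How often an adverse event is noticed depends on how often someone is in a position to notice it. Here one side of the exercise-versus-control comparison is seen, under supervision, three times as often as the other, and the recording rule is worded around an activity that controls do not undertake. If events come to light through these contacts, part of any excess in the exercise arms would reflect closer observation and not harm.

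A second loss concerns delayed events. The Termination criteria foresee serious effects during or after exercise, but no section describes active asking between sessions or during follow-up.

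This matters because the Discussion presents the trial as needed to clarify the efficacy and safety of LRE-BFR, and says that evidence on its cardiovascular safety is lacking. Participants and therapist are unblinded, so spontaneous reporting may also differ by arm. With 11 participants per arm, one or two events missed among controls would change the picture, and events not captured during the trial cannot be recovered in the analysis.

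**Working it through.** The article gives no adverse-event rate or detection rate, so there is no stated figure on ascertainment to reproduce. What can be checked is the number of scheduled contacts.

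**Inputs**
- Exercise sessions: 3 per week for 12 weeks, the same in both exercise arms (LRE-BFR, CRE, Table 2).
- Control education sessions: 1 per week for 12 weeks (Control group, Table 2).
- Diet calls: 3 per week (Nutritional intake). The 24-week period is attached to the requirement to keep dietary habits; that the calls run equally long is the natural reading, not an explicit statement.

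**Contacts (frequency × weeks)**

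| | Each exercise arm | Control |
|---|---|---|
| Sessions, weeks 1–12 | 3 × 12 = 36 | 1 × 12 = 12 |
| Sessions, weeks 13–24 | 0 | 0 |
| Diet calls, weeks 1–12 | 3 × 12 = 36 | 3 × 12 = 36 |
| Diet calls, weeks 1–24 | 3 × 24 = 72 | 3 × 24 = 72 |

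- Sessions alone in weeks 1–12: 36/12 = 3:1.
- Sessions plus calls in weeks 1–12: (36 + 36)/(12 + 36) = 72/48 = 1.5:1. This ratio applies only if the calls pick up adverse events, which the article does not say.
- LRE-BFR versus CRE: 36/36 = 1:1.
- Calls alone: 1:1 in every period.

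**Direction of the effect, under an assumption that is not in the article.** Suppose the true rate is equal in all arms, each session independently detects a short-lived event of that week with probability q, and the calls detect nothing. Weekly capture is then 1 − (1 − q)³ in an exercise arm and q in control.

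| q (assumed) | Exercise | Control | Ratio |
|---|---|---|---|
| 0.2 | 0.488 | 0.2 | 2.44 |
| 0.5 | 0.875 | 0.5 | 1.75 |
| 0.8 | 0.992 | 0.8 | 1.24 |

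The ratio exceeds 1 throughout and falls towards 1 as detection per contact improves. The table shows direction only; nothing in the article says which row applies.

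**After the fix.** One question per week gives 1 × 24 = 24 identical questions per participant in every arm, 12 of them in weeks 1–12, a ratio of 1:1.

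**The case against.** The strongest counter-argument is that this is silence in a condensed article. Event forms and question scripts commonly sit in the full protocol. Table 1 treats the arms alike, and the recording rule under Group protocols can be read as a time window, not a place of detection. This stands in part. The absence of a script is not the point; the point is that the stated features (3:1 session contact, wording built around exercise, an equal channel described only for diet) make unequal detection likely. Table 1 fixes when events are recorded, not how.

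A reader might infer that adverse effects are picked up mainly at exercise sessions, and that in weeks 13–24 they rest on recall at the week 24 visit. The article supports neither. The recording rule expressly covers follow-up, Table 1 schedules adverse events through week 24, and no method of ascertainment is stated for any arm.

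It is also fair that adverse events are listed under other measures and not as an outcome, that Statistical analysis names no between-arm test of them, and that the distortion would overstate harm from exercise and not hide it. These points limit the consequence. They do not remove it, because any tabulation of events by arm will be read as a comparison.

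Finally, the calls are made by researchers and community workers, whereas a dedicated investigator records adverse effects. That stands, and the fix must include a hand-off.

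**Conclusion.** The point holds as a proportionate improvement, not as an error in the plan. For exercise versus control in weeks 1–12, detection of adverse events is likely to be unequal, given 36 against 12 sessions and no described common way of asking. LRE-BFR versus CRE is untouched because session frequency is the same. In follow-up no arm has sessions, so the concern there is under-counting in all arms and not imbalance.

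A reader might want to attach a spurious risk ratio to this. The article does not allow it: every such figure rests on assumed detection rates, and the ratios of 1.24 to 2.44 above are illustrations of that kind. The conclusion rests on two assumptions: that more frequent supervised contact raises the chance that an event is noted, and that the full protocol does not already prescribe identical questioning in all arms.

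**What to change.** In Group protocols and Nutritional intake, add one fixed, identically worded adverse-event question (new or worse symptoms, injury, fall or medical contact, with start date) to one existing diet call per week in all three arms. Ask it for as long as the calls run, which is 24 weeks on the natural reading, and state that duration explicitly. Callers pass each answer to the dedicated investigator.

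Base any between-arm summary of adverse events on these answers plus the scheduled week 12 and week 24 assessments. Report events seen only at supervised sessions separately, for the two exercise arms.

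The cost is about a minute per weekly call. With 33 participants and 24 weeks that is at most 33 × 24 = 792 minutes, about 13 hours over the whole trial. Add a short briefing and hand-off for callers, and more minor events to log. No new contacts are needed. The change equalises how often people are asked; it does not remove differences in reporting that come from participants knowing their arm.
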